### Participant timeline {13}

The time schedule of enrollment, interventions, and assessments for the participants of this study is presented in Table 1. The flow chart of the study is shown in Fig. 1.

**Table 1 Tab1:** Checklist of enrolment, interventions, and assessments

	Study period										
	Enrolment	Allocation	Post-allocation								Close-out
Timepoint**	*-t*_*1*_	0	*t*_*1*_	*t*_*2*_	*t*_*3*_	*t*_*4*_	*t*_*5*_	*t*_*6*_	*t*_*7*_	*t*_*8*_	*t*_*9*_
**Enrolment:**											
**Eligibility screen**	X										
**Informed consent**	X										
**Allocation**		X									
**Interventions:**											
***ESPB***			X								
***Control***			X								
**Assessments:**											
***Baseline characteristics***	X	X									
***NRS for pain***						X	X	X	X	X	
***Hydromorphone consumption***									X	X	
***QoR-15***									X	X	
***Fentanyl requirements***				X							
***Rescue analgesics***											
***Adverse events***											
***Mortality***											X

**Fig. 1 Fig1:**
[figure not shown]
Flowchart of the trial. −t_1_, preoperative; t_1_, before induction of general anesthesia; t_2_, completion of surgery; t_3_, ICU admission; t_4_, 6 h after surgery; t_5_, 12 h after surgery; t_6_, 18 h after surgery; t_7_, 24 h after surgery; t_8_, 48 h after surgery days after surgery; t_9_, 30 days after surgery; ESPB, erector spinae plane block; NRS, numeric rating scale; QoR, quality of recovery

### Sample size {14}

Sample size is determined on the basis of a preliminary study to observe the efficacy of ESPB on MIDCAB patients within 12 h after surgery in our hospital. We use the PASS 11.0 software to calculate the sample size. We power the study to identify a relevant clinical difference of 1.5 in NRS score with a standard deviation (SD) of 1.9 [21]. Thus, to compare two means using repeated measures analysis of variance (ANOVA) method with a power of 90% and a level of significance of 5% (two sided), a sample size of 46 patients is estimated in this study. Considering possible dropouts, a sample size of 60 patients will be required.

### Recruitment {15}

The principal investigator is responsible for patient recruitment. Every potential participant will be visited by investigator 1 day before operation in the ward and provided with details of the study, including study backgrounds, protocol, possible benefits and risks other medical choices, right to participate and withdraw, and use of individual information and data.

## Assignment of interventions: allocation

### Sequence generation {16a}

According to a computer-generated random number, patients will be allocated to either the ESPB group or the control group at a 1:1 ratio.

### Concealment mechanism {16b}

The group assignments will be sealed in sequentially numbered opaque envelopes and locked in a cabinet in the research office. Randomization information will not be unveiled until the envelope is opened.

### Implementation {16c}

A nurse anesthetist who is not involved in the treatment, evaluation, data collection, or statistical analysis will generate the allocation sequence. The nurse anesthetist will open the envelope 1 h prior to surgery and prepare the study medications accordingly. The study medications are 0.5% ropivacaine 30 mL for the ESPB group and 0.9% normal saline for the control group. Both syringes would be identical and will be labeled as “study medication” to ensure the blinding procedure.

## Assignment of interventions: blinding

### Who will be blinded {17a}

All participants will be blinded to group allocations. The anesthesiologists who will perform the block and those who will provide intraoperative care are blinded. A blinded investigator will collect the perioperative data. The cardiac surgeons and medical staff in cardiac ICU and the ward will be unaware of the group allocations.

### Procedure for unblinding if needed {17b}

In case of medical necessity or emergency related to the procedure, the principal investigator could decide to unblind and inform the patient and attending medical staff.

### Plans to promote participant retention and complete follow-up {18b}

The investigators will make best effort to do a close follow-up and good communication with the participants throughout the study period. The participants will be provided with detailed study timeline before data collection and forenotice of the upcoming follow-up visit. Any question or concern related to the study and clinical treatment from the participants will be responded patiently in detail.

### Confidentiality {27}

All the electronic data and paper documents will be securely stored in the hospital’s information system and a locked file storage cabinet respectively for at least 5 years after the completion of the study. Only the investigators will be authorized to get access to the study dataset. The participants’ personal identifying information will be replaced by study identification codes for confidentiality.

### Plans for collection, laboratory evaluation, and storage of biological specimens for genetic or molecular analysis in this trial/future use {33}

Not applicable. There are no relevant plans since no biological specimens will be involved in the present trial.

## Statistical methods

### Statistical methods for primary and secondary outcomes {20a}

Statistical analysis will be done using SPSS Statistics (IBM: V. 24). Before analysis, the normality of the data distribution will be assessed using the Shapiro–Wilk test and Q–Q plots. For postoperative NRS scores, we will use repeated measurement with post hoc testing. For the other outcomes, postoperative hydromorphone consumption, QoR-15 scale, intraoperative fentanyl requirements, time to tracheal extubation and chest tube removal after surgery, LOS in ICU, and hospital discharge time will be analyzed with the independent samples *t* test or Mann–Whitney *U* test. The incidence of PONV, POCD, additional use of postoperative rescue analgesics, and 30-day mortality will be compared by the *χ*^2^ or Fisher’s exact test when necessary. All *P* values will be two sided, and statistical differences will be defined as less than 0.05. Missing data will be handled with multiple imputation methods.

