## Abstract

**Background:**

Minimally invasive direct coronary artery bypass (MIDCAB) surgery offers an effective option for coronary artery disease (CAD) patients with the avoidance of median sternotomy and fast postoperative recovery. However, MIDCAB is still associated with significant postoperative pain which may lead to delayed recovery. The erector spinae plane block (ESPB) is a superficial fascial plane block. There have not been randomized controlled trials evaluating the effects of ESPB on analgesia and patient recovery following MIDCAB surgery. We therefore designed a double-blind prospective randomized placebo-controlled trial, aiming to prove the hypothesis that ESPB reduces postoperative pain scores in patients undergoing MIDCAB surgery.

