**Methods:**

The study protocol has been reviewed and approved by the Ethical Review Committee of Peking University People’s Hospital. Sixty adult patients of either sex scheduled for MIDCAB surgery under general anesthesia (GA) will be included. Patients will be randomly allocated to receive either a preoperative single-shot ESPB with 30 mL of ropivacaine 0.5% (ESPB group) or normal saline 0.9% (control group). The primary outcomes are the difference between the two groups in numeric rating scale (NRS) scores at rest at different time points (6, 12, 18, 24, 48 h) after surgery. The secondary outcomes include NRS scores on deep inspiration within 48 h, postoperative hydromorphone consumption, and quality of patient recovery at 24 h and 48 h, using the Quality of Recovery-15 (QoR-15) scale. The other outcomes include intraoperative fentanyl requirements, the need for additional postoperative rescue analgesics, time to tracheal extubation and chest tube removal after surgery, incidence of postoperative nausea and vomiting (PONV) and postoperative cognitive dysfunction (POCD), intensive care unit (ICU) length of stay (LOS), hospital discharge time, and 30-day mortality. Adverse events will be also evaluated.

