### Trial design {8}

We are conducting a single-center, parallel-group, randomized controlled exploratory trial, with a 1:1 allocation of participants randomized to the intervention and control groups.

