### Outcomes {12}

The primary outcome is pain intensity measured by the NRS score at rest at different time points (6, 12, 18, 24, 48 h) after MIDCAB. The NRS is a self-reported 11-point scale representing different degrees of pain. The number 0 represents painless, while 10 represents worst pain ever. The intensity of pain can be categorized into mild (1 to 3), moderate (4 to 6), and severe (7 to 10). The secondary outcomes are NRS scores on deep inspiration within 48 h after surgery, postoperative 48 h hydromorphone consumption, and quality of patient recovery at 24 h and 48 h, assessed by the Quality of Recovery-15 (QoR-15) scale. Other outcomes include intraoperative fentanyl requirements, additional use of postoperative rescue analgesics, time to tracheal extubation and chest tube removal after surgery, LOS in ICU, and hospital discharge time. Adverse events including PONV, postoperative cognitive dysfunction (POCD), atrial fibrillation, pleural effusion, pericarditis, and block-related complications, for instance, hematoma, pneumothorax, and infection, will be recorded. Thirty-day mortality will also be evaluated as a safety outcome.

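### The protocol does not say which repeated-measures effect or hour decides the primary outcome, so the false positive chance runs from 5% to about 13–21% depending on an unwritten choice

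*Protocol article*

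**What the plan says.** Four places in the protocol article bear on the primary test.

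- **What is primary.** The Abstract (Methods) uses the plural: "The primary outcomes are the difference between the two groups in numeric rating scale (NRS) scores at rest at different time points", followed by 6, 12, 18, 24 and 48 h. Outcomes {12} lists the same five hours in the singular: "The primary outcome is pain intensity measured by the NRS score at rest at different time points". Neither ranks the hours.
- **How it is analysed.** Statistical methods {20a}: "For postoperative NRS scores, we will use repeated measurement with post hoc testing". The same section sets one threshold for all P values: "values will be two sided, and statistical differences will be defined as less than 0.05".
- **What the sample size assumes.** Sample size {14} takes a difference of 1.5, an SD of 1.9, 90% power and a two-sided 5% level, and sets out "to compare two means using repeated measures analysis of variance (ANOVA) method". It arrives at 46 patients, raised to 60 for dropouts.
- **What kind of trial it is.** Trial design {8} calls it a "randomized controlled exploratory trial", while the Abstract (Background) describes it as "aiming to prove the hypothesis that ESPB reduces postoperative pain scores".

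**The concern.** A two-group repeated-measures analysis yields several P values that bear on treatment: the group effect, the group-by-time effect and, through post hoc tests, a comparison at each of the five hours. The protocol attaches its 0.05 threshold to all of them and does not name the one that decides. Read with the plural wording of the Abstract, a P value below 0.05 at one hour could be reported as a positive result on a primary outcome.

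Mixed results are foreseeable. The block is a single injection, and the preliminary study behind the sample size looked only at the first 12 h, whereas the primary outcome runs to 48 h. A difference at 6 h that is gone later would leave the group effect, the interaction and the hourly tests in disagreement. The protocol then has no rule for the conclusion, and the choice would fall after the data are seen. A 5% design level has no clear meaning until the test it applies to is named.

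**Working it through.** **Inputs from the protocol.** Five assessments (Outcomes {12}); 0.05 two-sided for every P value (Statistical methods {20a}); difference 1.5, SD 1.9, power 90%, level 5% two-sided, 46 evaluable and 60 enrolled (Sample size {14}); 1:1 allocation (Trial design {8}), hence 23 and 30 per arm.

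**Assumed.** The correlation ρ between assessments is not given. I use 0.3 to 0.8 as the main range and show 0 and 0.9 as extremes.

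**Step 1: what the 46 implies about the intended test.** For one comparison of means at one time:

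n per arm = 2 × [1.9 × (1.960 + 1.282) / 1.5]² = 33.7, rounded up to 34, or 68 in total (35 per arm, 70 in total, with the t distribution).

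For the mean of m equally correlated measures, multiply by (1 + (m − 1)ρ)/m. With m = 5:

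- ρ = 0.5: 33.7 × 0.60 = 20.2, so 21 per arm, 42 in total
- ρ = 0.6: 33.7 × 0.68 = 22.9, so 23 per arm, **46 in total**
- ρ = 0.7: 33.7 × 0.76 = 25.6, so 26 per arm, 52 in total

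The 46 cannot be reproduced from the printed inputs alone, but it fits a group contrast averaged over five assessments at ρ of about 0.6. (Three measures at ρ of about 0.5 would also give 46.) It does not fit a test at one hour.

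**Step 2: false positive chance under each decision rule.** With five independent tests at 0.05, the chance of at least one false positive is 1 − 0.95⁵ = 22.6%. With correlated assessments I take it from simulation under no effect at any hour: 30 per arm, normal outcomes, equal correlation, 40,000 trials per setting. Monte Carlo standard error is about 0.1 to 0.2 percentage points.

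| Rule for a positive primary claim | ρ = 0.3 | ρ = 0.5 | ρ = 0.6 | ρ = 0.8 | ρ = 0.9 |
|---|---|---|---|---|---|
| Group effect only | 5.0% | 5.0% | 5.0% | 5.0% | 5.2% |
| Any hour, but only after a significant group effect | 4.5% | 4.7% | 4.9% | 5.0% | 5.2% |
| Any hour, after a significant group or interaction effect | 8.1% | 7.4% | 7.1% | 6.1% | 5.8% |
| Group or interaction effect | 9.9% | 9.6% | 9.7% | 9.7% | 10.0% |
| Any hour, unadjusted | 21.1% | 18.3% | 16.9% | 12.8% | 10.3% |
| Any hour at 0.05/5 = 0.01 | 4.6% | 4.0% | 4.1% | 3.0% | 2.5% |

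If correlation instead decays with distance between assessments (first-order autoregressive), the any-hour rule gives 21.8% at 0.3 and 15.0% at 0.8. The group-or-interaction rule then gives 10.3% at 0.3 and 12.1% at 0.8. Part of that excess over 1 − 0.95² = 9.75% arises because the interaction test was run without a sphericity correction.

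**Step 3: match the rules to the text.** The protocol selects none of these rows. Sample size {14} points towards the first row, the plural in the Abstract towards the fifth, and the mention of post hoc tests in {20a} fits the second and third.

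**The case against.** The strongest reply is that the any-hour rule is not in the protocol. Both the sample size and the analysis section specify a repeated-measures method, and post hoc tests ordinarily follow an overall test. Outcomes {12} and the Discussion treat resting NRS as one outcome followed over time, and Objectives {7} frames the goal as analgesia over 48 h. On that reading the primary test is the group effect and its error rate is 5%. Correction of post hoc tests is also a detail commonly left to an analysis plan, which is not shown here, and a 0.05 threshold is compatible with adjusted P values.

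Most of this stands, and it rules out three stronger inferences:

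- A reader might conclude that the trial's false positive rate is 13–21%. The documents do not support that: the figure belongs to one possible rule, and to correlations that I have assumed.
- A reader might conclude that the sample size rests on a single-time comparison at odds with the analysis. It does not: the section names repeated measures ANOVA, and 46 is well below the 68 that a single comparison needs.
- A reader might conclude that the post hoc tests are unadjusted. The text is silent on this.

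The reply does not remove the gap. Which comparison decides the primary outcome belongs in the protocol, and the Abstract's wording pulls away from the single-effect reading. The exploratory label lowers the stakes, but it supplies no decision rule and sits beside an aim to prove a hypothesis with 90% power at a two-sided 5% level.

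**Conclusion.** The point holds as a failure to fix the primary test, not as a demonstrated inflation of error. The chance of a false positive primary claim is 5% if the group effect alone decides. It is about 10–12% if either the group or the interaction effect is accepted. On the any-hour reading it can reach about 13–21%, roughly 2.5 to 4 times the design level.

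The last range assumes normal outcomes, no effect at any hour, unadjusted hourly tests and correlations of 0.3 to 0.8; it would be 22.6% under independence and about 10% at 0.9. The 5% figure for the group effect does not depend on the correlation. Severity: should-fix.

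**What to change.** In the Abstract (Methods), Outcomes {12} and Statistical methods {20a}, use the singular and name one primary test: the between-group contrast in resting NRS averaged over the five assessments, that is, the group effect of the repeated-measures model, at two-sided 0.05. This agrees with Sample size {14}.

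Test individual hours only if that contrast is significant, and with a stated multiplicity adjustment; otherwise report them as estimates with confidence intervals. The adjustment is needed in addition to the gate. If a real effect at one hour opens the gate, four unadjusted tests at null hours still carry up to 1 − 0.95⁴ = 18.5% if independent. The choice of adjustment and the exact form of the model are matters of preference and can sit in the analysis plan.

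The cost is a few lines of wording, submitted as an amendment to the ethics committee and made before unblinding, with no new data. Single-hour claims become harder to make. Averaging also dilutes a short-lived effect: a difference of 1.5 at two of the five assessments and none at the rest averages 2 × 1.5 / 5 = 0.6. If the sponsor prefers another single contrast for that reason, it would hold the 5% equally well, but the sample size would need to be rechecked for it.

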### Interim analyses {21b}

Not applicable. No interim analysis is planned for the present trial.

### Methods for additional analyses (e.g., subgroup analyses) {20b}

Not applicable. There are no subgroup analyses planned.

### Methods in analysis to handle protocol non-adherence and any statistical methods to handle missing data {20c}

Data will be analyzed by both intention-to-treat and per-protocol principals. Missing data will be handled with multiple imputation methods.

### Plans to give access to the full protocol, participant level-data and statistical code {31c}

The corresponding author can be contacted for sharing participant-level dataset upon reasonable request.

### Composition of the data monitoring committee, its role and reporting structure {21a}

The data monitoring committee will be composed of the Ethical Review Committee of Peking University People’s Hospital, which is independent of the sponsor and competing interests. Data quality reporting will be conducted by the principal investigator.

### Adverse event reporting and harms {22}

In the present study, we define serious adverse events (SAEs) as one of the following criteria: patient death or any life-threatening conditions and persistent or significant disability. SAEs will be reported within 24 h to the quality and safety control committee and the ethics committee of our hospital. All adverse events related to this study will be recorded and reported to the ethics committee by the principal investigator within 1 week.

Systemic toxicity of local anesthetic, pneumothorax, hematoma, and injection site infection will be continuously inspected by physical examination, X-ray, and/or ultrasound in the operating room and ICU after the administration of study medication. Ultrasound guidance, negative aspiration for blood before local anesthetic injection, and low-speed administration of local anesthetic will be used to help prevent the occurrence of pneumothorax, hematoma, and systemic toxicity of local anesthetic.

### Frequency and plans for auditing trial conduct {23}

The research team will meet monthly to check the trial progress and discuss any issues that will be encountered during trial conduct. The trial conduct will be audited every 6 months by the Ethical Review Committee of Peking University People’s Hospital.

### Plans for communicating important protocol amendments to relevant parties (e.g., trial participants, ethical committees) {25}

Any amendment to the study protocol, informed consent, or other related documents will also be asked for approval by the ethics committee.

### Dissemination plans {31a}

The results of this study will be disseminated via academic conference presentations and publication in peer-reviewed journals. The findings and conclusions will be shared with all the participants upon completion of the study. The principal investigator of the study will be the lead author. The investigators that have taken part in the study for at least 3 months and contributed to the manuscript drafting will be listed in the authorship.

## Discussion

As more minimally invasive cardiac surgeries are being performed in recent years, the need for better postoperative pain management and faster recovery has become a pressing concern. Although the incision is smaller, MIDCAB surgery can still cause moderate to severe postoperative pain which could make the patient’s breathing shallow and irritating and result in increased risk of postoperative pulmonary complications (PPCs). PPCs may impede early recovery and are associated with prolonged hospital LOS and increased mortality following cardiac surgery [24, 25]. Therefore, optimizing analgesic regimen with multimodal approaches to achieve adequate pain relief following MIDCAB surgery is a crucial consideration.

In our hospital, ESPB has been successfully applied in thoracic and lumbar spinal surgeries for analgesia and its safety profile has been well documented in these studies [26, 27]. In addition, the volume and concentration of the study medication have been safely used in previous studies without any block-related complications reported [12, 28]. However, although the efficacy of bilateral ESPB has been demonstrated in adult cardiac surgery with midline thoracotomy, it is still unclear whether this technique is effective and beneficial for MIDCAB patients. Thus, we designed this randomized controlled study and expect to fill in a gap in the existing literature. The postoperative resting NRS score is the primary outcome and being measured at different time points during the first 48 h after surgery to better delineate pain intensity patterns. Additionally, perioperative opioid consumption and associated side effects as well as early postoperative recovery outcomes are also being measured. We anticipate that the findings of our study would help to clarify the impact of ESPB on analgesia and patient recovery following MIDCAB surgery and may also help to optimize analgesic regimen in this specific population.

We also foresee some limitations in this study. For instance, patients who have accidental prolonged progress after surgery may be unable to complete the NRS assessment at predetermined time points. As a result, a certain lost to follow-up bias cannot be ruled out. In addition, the dermatomal distribution of ESPB is not tested, and the optimal volume and concentration of ESPB is unevaluated, emphasizing the need for further investigations.

